## Methods: participants, interventions and outcomes

### Setting, recruitment and eligibility criteria

Data collection will be conducted at the Interdisciplinary Memory Clinic (IDMC) in Bern and the Cantonal Hospital of Lucerne, Switzerland. Participants will be recruited by local newspaper adverts as well as directly through the respective Memory Clinic. A total of 162 elderly participants (*n* = 54 per study arm) from a continuum covering cognitively normal individuals at risk for AD with SCD to MCI (diagnosed or cut-off score in the cognitive telephone screening instrument (COGTEL) according to Alexopoulos [42]) and mild AD patients will be recruited. All participants will need to fulfill the following inclusion criteria: (1.) Ability to give their written consent to participate in the study; (2.) Age between 60 and 85 years; (3.) Native or fluent proficiency in German; (4.) Normal or corrected to normal vision and hearing; (5.) Ability to visit the study location repeatedly; (6.) MoCA (Montreal Cognitive Assessment [43] > 11. Exclusion criteria are patients with any contra-indications for MRI-scanning, substance abuse or severe medical conditions (of note: patients with mild depressive symptoms not fulfilling criteria for major depressive disorder are recruited into the sample to better represent clinical reality).

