### Statistical methods

#### Sample size

For our primary analysis (“Does change in performance on the three typical AD domains 3 months after the start of the training differ between groups?”), a repeated- measures ANOVA is planned (3 groups with 2 time points). We computed the necessary sample size using G*Power [66] to ensure a power of 80% to detect an assumed moderate effect (i.e. effect size: η2 = 0.06, f = 0.25) with α of 5%. The power analysis revealed a total sample size of 162 (54 participants per group). Moreover, we performed a power analysis for testing the interaction between the groups and all four time points within a repeated-measures ANOVA using the same parameters as before (α = 5%, power = 80%, η2 = 0.06) as well as a non-sphericity correction factor of 0.75. According to this power analysis a total sample size of 96 (32 participants per group) is needed.

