#### Statistical methods for primary and secondary outcomes

Primary outcomes are three composite scores corresponding to the domains mostly affected by AD. One advantage of composite scores is a reduced number of statistical tests. At the same time, separate composite scores for the three domains allow to assess and compare changes in the scores individually. For each of the domains, three variables will be included in the composite score (EM: AVLT learning sum, immediate and delayed recall; SA: ROCF encoding, immediate and delayed recall; semantics: semantic fluency from the MoCA, phonemic fluency and GNT). We will perform a principal component analysis (PCA) for each of the respective domains.

All scores will be scaled and centralized on the scores from the baseline assessment and weighted if appropriate according to their loadings in the PCA. The main hypothesis will be tested with a repeated-measures ANOVA for which an adequate level of power should be guaranteed (according to the power analysis described before). Further analyses (using all time points and additional numeric subject characteristics as predictor variables) will be performed with linear mixed models as they allow for more sophisticated model design and a better handling of missing data. As covariates, the factors study site and study arm will be included in all analyses. Neuroimaging data will be analyzed with SPM12 and related toolboxes (e.g., Functional Connectivity (CONN) toolbox [67]). Apart from task related fMRI, resting state fMRI, volumetrical images and ASL will be performed.

To assure meaningful data, non-adherence to the training regimen leads to exclusion of further analysis. Non-adherence is defined as completing less than 50% of the required training sessions and attendance of less than 70% of the group sessions.

Given that a relatively high number of games are purposely built for this study, we expect the need for continuous adjustments based on feedback from participants. Should substantial adjustments be necessary, we will introduce release number as a covariate in the analysis.

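### The 162 participants needed for 80% power are also the 162 to be recruited, so the stated power holds only if almost nobody is lost from the primary analysis

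*Protocol article*

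**What the plan says.** Under Sample size, the primary question is whether change 3 months after the start of training differs between groups. A "repeated- measures ANOVA is planned (3 groups with 2 time points") is specified, with "effect size: η2 = 0.06, f = 0.25" and "with α of 5"%, and the sample size is computed "to ensure a power of 80% to detect an assumed moderate effect". The result: "The power analysis revealed a total sample size of 162 (54 participants per group"). A second calculation for all four time points, with a non-sphericity correction of 0.75, gives 96.

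Under Setting, recruitment and eligibility criteria, the recruitment figure is identical: "A total of 162 elderly participants", 54 per arm. The abstract also plans 162.

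Under Statistical methods for primary and secondary outcomes, three statements bear on how many of the 162 will be analysed:

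- "The main hypothesis will be tested with a repeated-measures ANOVA for which an adequate level of power should be guaranteed", with a reference back to the power analysis.
- Further analyses will use "linear mixed models as they allow for more sophisticated model design and a better handling of missing data".
- Participants who do not adhere to the training regimen are excluded from analysis. Non-adherence means completing under 50% of the required training sessions and attending under 70% of the group sessions.

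**The concern.** A power calculation gives the number to be analysed. Here that number is also the number to be enrolled, although the same article has a rule that can remove participants and a primary test that cannot use anyone without the second assessment. The four statements (number needed, number recruited, exclusion rule, assurance of power) agree only if loss is close to nil.

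The article gives reasons to expect some loss. Participants are aged 60 to 85 and range up to mild AD. They are asked for daily sessions and weekly on-site meetings over 10 weeks, and the section on adherence strategies says that earlier studies of this kind often had adherence problems.

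At stake is the reading of a null result. A reader would take it as coming from a trial with 80% power for a moderate effect, when the power could be nearer 70 to 76%. In addition, removal after randomisation need not fall equally on the arms: the waitlist arm has no training to adhere to before the second assessment.

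**Working it through.** **Inputs.** From Sample size: k = 3 groups, m = 2 time points, f = 0.25 (f² = 0.0625), α = 0.05, target power 0.80. From the recruitment section: N = 162. The loss rates are assumptions, because the article states none.

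**Formula.** Group-by-time interaction, noncentral F:

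- df1 = (k − 1)(m − 1)ε
- df2 = (N − k)(m − 1)ε
- λ = f²(N − k)(m − 1)ε
- power = P(F′(df1, df2, λ) > F at the 0.95 quantile)

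This is the G*Power option that takes the effect size as SPSS defines it. The article does not name the option, so it was identified by checking which one returns the article's figures.

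**Reproducing the article's figures.**

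- Two time points (ε = 1): the smallest N with power of at least 0.80 is 161, or 162 in three equal groups. At N = 162, λ = 0.0625 × 159 = 9.94, df = 2 and 159, and power = 0.805.
- Four time points (ε = 0.75): the smallest N is 94, or 96 in three equal groups, with power 0.813.

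Both stated figures are matched. Other options do not match: with λ = f²N the two-time-point answer is 159 in equal groups, and the G*Power default with an assumed correlation of 0.5 gives 42. So 162 contains no hidden reserve beyond rounding 161 up to a multiple of three.

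**Power by number analysed** (m = 2, so λ = 0.0625 × (N − 3), df = 2 and N − 3):

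| Assumed loss | N analysed | λ | Power |
|---|---|---|---|
| 0% | 162 | 9.94 | 80.5% |
| 5% | 154 | 9.44 | 78.3% |
| 10% | 146 | 8.94 | 75.8% |
| 15% | 138 | 8.44 | 73.2% |
| 20% | 130 | 7.94 | 70.3% |

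**Sensitivity to the effect size.** The article gives both η² = 0.06 and f = 0.25, which are not quite the same: f² = 0.06/0.94 = 0.0638, so f = 0.253. With the unrounded value, power is 81.4% at 162, 76.8% at 146, 74.1% at 138 and 71.3% at 130, about one percentage point higher throughout.

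**For scale.** To keep 162 analysable, N/(1 − d) would be 180 at 10% loss, 191 at 15% and 203 at 20%.

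**The case against.** Several points on the other side are sound.

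- **Nothing is miscalculated.** Both 162 and 96 reproduce. What is missing is a margin.
- **A reader might infer that power is lost once two participants are missing.** At N = 160 it is 79.96%, which is 80.0% to one decimal. With η² = 0.06 unrounded, it falls below 80% only at the sixth loss (80.02% at 157, 79.74% at 156). The exact crossing point carries no weight.
- **A reader might infer that the plan's own rules guarantee loss.** They do not. The exclusion rule is conditional and joins its two criteria with *and*, so it could remove nobody. Its wording also leaves some doubt whether it covers the primary ANOVA or only later analyses. The remark about poor adherence describes earlier studies and introduces this trial's countermeasures. Loss is likely, not certain.
- **Complete-case analysis is not stated.** It is an inference, but a safe one: a two-time-point repeated-measures ANOVA needs both values, and the article itself prefers mixed models where data are missing. The handling of missing data might be set out in a document not shown.
- **The loss rates are assumed and the effect size is conventional.** With 146 analysed the trial keeps 80% power for f = 0.262, and with 130 for f = 0.279. These are small shifts from 0.25.

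These points limit the size of the concern but do not remove it. The article prints the number needed, an equal number recruited, an exclusion rule and an assurance of power, and these do not fit together whatever a fuller document may add.

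If loss fell only on the CCT and active control arms, power would also depend on the pattern of group means, which the article does not give. No single range can be quoted for that case.

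**Conclusion.** The concern holds as a missing margin, not as an arithmetic error. The stated 80% applies to 162 analysed participants, and 162 is also all that will be recruited. On the option that reproduces both published sample sizes, power for f = 0.25 at α = 5% is about 76%, 73% and 70% at losses of 10%, 15% and 20%. These figures assume loss spread evenly over the arms and a primary analysis restricted to participants with both assessments. The assurance of adequate power is stronger than the design supports. Whether the shortfall proves material depends on retention, which the article does not project.

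**What to change.** Keep enrolment at 162 and change two things in the text.

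1. Under Sample size, state power for the number expected to be analysed, for example: *162 randomised; about 76% / 73% / 70% power at 10 / 15 / 20% loss*. Under Statistical methods, remove the word guaranteed.
2. Run the primary group-by-time test in the linear mixed model already planned for further analyses, with all randomised participants who have assessments, including non-adherers who attend the second one.

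The second change reduces exclusion after randomisation and keeps those non-adherers in the comparison. It should not be presented as restoring the power: a participant with only a baseline adds almost nothing to the group-by-time contrast, and retained non-adherers may dilute the effect.

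The cost is a few sentences and a lower printed power figure. The article reports recruitment as ongoing, so the change can be made before the analysis.

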#### Statistical methods for primary and secondary outcomes

Primary outcomes are three composite scores corresponding to the domains mostly affected by AD. One advantage of composite scores is a reduced number of statistical tests. At the same time, separate composite scores for the three domains allow to assess and compare changes in the scores individually. For each of the domains, three variables will be included in the composite score (EM: AVLT learning sum, immediate and delayed recall; SA: ROCF encoding, immediate and delayed recall; semantics: semantic fluency from the MoCA, phonemic fluency and GNT). We will perform a principal component analysis (PCA) for each of the respective domains.

All scores will be scaled and centralized on the scores from the baseline assessment and weighted if appropriate according to their loadings in the PCA. The main hypothesis will be tested with a repeated-measures ANOVA for which an adequate level of power should be guaranteed (according to the power analysis described before). Further analyses (using all time points and additional numeric subject characteristics as predictor variables) will be performed with linear mixed models as they allow for more sophisticated model design and a better handling of missing data. As covariates, the factors study site and study arm will be included in all analyses. Neuroimaging data will be analyzed with SPM12 and related toolboxes (e.g., Functional Connectivity (CONN) toolbox [67]). Apart from task related fMRI, resting state fMRI, volumetrical images and ASL will be performed.

To assure meaningful data, non-adherence to the training regimen leads to exclusion of further analysis. Non-adherence is defined as completing less than 50% of the required training sessions and attendance of less than 70% of the group sessions.

Given that a relatively high number of games are purposely built for this study, we expect the need for continuous adjustments based on feedback from participants. Should substantial adjustments be necessary, we will introduce release number as a covariate in the analysis.

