**Methods:**

In this bi-centric, randomized controlled trial (RCT) with parallel groups, participants (planned *N* = 162, aged 60–85 years) at risk for AD and with at least subjective cognitive decline will be randomized to one of three groups. We will compare serious game-based CCT against a passive wait list control condition and an active control condition (watching documentaries). Training will consist of daily at-home sessions for 10 weeks (50 sessions) and weekly on-site group meetings. Subsequently, the CCT group will continue at-home training for an additional twenty-weeks including monthly on-site booster sessions. Investigators conducting the cognitive assessments will be blinded. Group leaders will be aware of participants’ group allocations. Primarily, we will evaluate change using a compound value derived from the comprehensive cognitive assessment for each of three cognitive domains. Secondary, longitudinal functional and structural magnetic resonance imaging (MRI) and evaluation of blood-based biomarkers will serve to investigate neuronal underpinnings of expected training benefits.

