### Outcomes

Each participant will perform the cognitive assessments four times in intervals of approximately 10 weeks. The individual cognitive profile will be assessed through a set of paper-pencil and tablet-based cognitive tests designed to evaluate typical AD components. More precisely, the general cognitive performance will be assessed in a paper-pencil version of the MoCA. The following tests will be administered as tablet-based versions: the auditory verbal learning test (AVLT) [56] to assess episodic memory, the Rey-Osterrieth Complex Figure Test (ROCF) [57] for spatial abilities/memory, and verbal fluency as well as the Graded Naming Task (GNT-30) [58] will be used to probe semantic memory. Additionally, participants will performed the Flanker Test [59] to assess attention/response inhibition abilities and the digit span test (forward and backwards) as measure of short-term memory and working memory respectively. Parallel versions of the tests will be used whenever possible. Based on this comprehensive test battery, a cognitive composite score will be calculated as primary outcome of cognitive performance.

Moreover, participants will be asked to complete questionnaires to assess their form of the day, their situational motivation [60], quality of life [61] and depressive symptoms trough the geriatric depression scale (GDS) [62]. Through in-house designed or adapted questionnaires, participants’ expectancy towards the cognitive training (Additional file 3) [63], and subjective cognitive performance (Additional file 4) will be assessed. Subjective cognitive performance will additionally be assessed in an informant rated version of the questionnaire (filled out by a close friend or relative) (Additional file 5). Unexperienced participants will have the opportunity to get used to the tablet and to have one on one support from the investigator before the training starts.

The mentioned tests will be supplemented by a set of paper-pencil based questionnaires that will be sent to the participants before the first on-site meeting. These preliminary questionnaires asses activities of daily living [64], handedness [65], and the informant rated subjective memory performance questionnaire.

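### The primary outcome is one composite in one section and three domain composites in others, and the sample size of 162 gives 80% power only for a single test at an unadjusted 5%

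*Protocol article*

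**What the plan says.** The article describes the primary outcome in three places.

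- **Abstract, Methods:** change will be evaluated with "a compound value derived from the comprehensive cognitive assessment for each of three cognitive domains". That is three outcomes.
- **Outcomes:** after listing the whole battery, including the MoCA, the Flanker test and digit span, it says that "a cognitive composite score will be calculated as primary outcome of cognitive performance". That is one outcome.
- **Statistical methods for primary and secondary outcomes:** "Primary outcomes are three composite scores corresponding to the domains mostly affected by AD". Three variables are named for each domain, nine in all, and neither Flanker nor digit span is among them. It adds that "separate composite scores for the three domains allow to assess and compare changes in the scores individually", and that using composites keeps the number of tests down.

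The Sample size section poses one question about the three domains and says that "a repeated- measures ANOVA is planned (3 groups with 2 time points"). The calculation is meant "to ensure a power of 80% to detect an assumed moderate effect (i.e. effect size: η2 = 0.06, f = 0.25) with α of 5" per cent, and "The power analysis revealed a total sample size of 162 (54 participants per group"). A second calculation covers all four time points: "According to this power analysis a total sample size of 96 (32 participants per group) is needed". The statistical section then relies on the first calculation for the power of the main hypothesis.

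**The concern.** The Outcomes section differs from the other two in both number and content: one score from the whole battery, against three scores from nine named variables. A reader cannot tell from the article which result decides whether the trial is positive.

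The sample size rests on one test at one significance level. With three primary outcomes, a 5% error rate and 80% power cannot both be taken from that calculation without a rule for combining the three results. Depending on the rule, either the overall error rate or the power differs from what the article states.

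**Working it through.** **Inputs.** From the Sample size section: 3 arms, 2 time points, f = 0.25 (so f² = 0.0625), α = 0.05, target power 0.80, N = 162 (54 per arm); for the second calculation, 4 time points and a non-sphericity factor of 0.75. From the statistical section: 3 primary composites. Not in the documents, so assumed: the correlation between the composites' change scores (0 to 0.9 shown) and the success rule.

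**Step 1. Reproduce the stated figures.** For the interaction, take df1 = (k−1)(m−1)ε, df2 = (N−k)(m−1)ε and noncentrality λ = f²(N−k)(m−1)ε.

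- Two time points, N = 162: df = 2 and 159, λ = 0.0625 × 159 = 9.94, power **0.805**. The next smaller balanced total, 159, gives 0.797. So 162 is reproduced.
- Four time points, N = 96: df1 = 2 × 3 × 0.75 = 4.5, df2 = 93 × 3 × 0.75 = 209.25, λ = 0.0625 × 209.25 = 13.08, power 0.813. The smallest total is 94, which rounds to 96 for equal arms. So 96 is reproduced as well.

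The same convention gives both figures, so 162 is the answer for one outcome at α = 0.05.

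**Step 2. Error rate if any one of three sufficed, each at 5%.** Independent tests: 1 − 0.95³ = 0.143. Upper bound for any dependence: 3 × 0.05 = 0.15.

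**Step 3. Power at a Bonferroni level.** α = 0.05/3 = 0.0167, N = 162: power per domain **0.663**. For 80% per domain at this level, 207 participants give 0.798 and 210 give 0.805.

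**Step 4. Power if all three must succeed.** Independent: 0.805³ = 0.522. With the alternative convention λ = f²N, power per test is 0.813 and 0.813³ = 0.537.

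**Step 5. Correlated composites.** With two time points, the interaction test equals a one-way ANOVA on change scores. Simulation with 54 per arm and 40,000 replicates per row; for the power columns, f = 0.25 in all three domains with the training arm differing from two equal control arms:

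| Correlation | Error, any of three at 5% | Power, all three at 5% | Bonferroni, at least one | Holm, each domain |
|---|---|---|---|---|
| 0 | 14.2% | 52% | 96% | 76% |
| 0.3 | 13.8% | 58% | 92% | 75% |
| 0.5 | 12.6% | 61% | 88% | 74% |
| 0.7 | 11.0% | 66% | 84% | 74% |
| 0.9 | 8.6% | 73% | 77% | 72% |

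Under λ = f²N the power figures are up to about two points higher, so Holm gives roughly 72–77% per domain over both conventions. The 66% of Step 3 is the floor: it is the power at the first Holm step, whatever happens in the other two domains.

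**The case against.** A reader might infer that the plan tests each composite at 5%, has no multiplicity control, and so carries a false-positive rate of about 15%. The article does not support that.

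- Both descriptions of the primary test are in the singular, and the research question covers the three domains together. Separate tests at 5% are a plausible reading, not a stated one.
- No passage says that one significant domain is enough. If all three were required, the family-wise error would not exceed 5%.
- The correlation between composites is not given. 15% is only the upper bound; independence gives 14.3%, and positive correlation lowers it.
- This is a condensed article. A multiplicity procedure may stand in an analysis plan that is not shown, so its absence here is not in itself a fault.
- Per-domain power is not the only yardstick. If one domain sufficed and all three effects were f = 0.25, the Bonferroni-adjusted chance of at least one success at 162 would be 77–96%.
- The single composite may be loose wording, since the other sections point to three domains and only those have listed components. To say that the primary could be picked after seeing results therefore goes further than the text needs.

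These objections remove the flat error-rate claim. They do not remove the conflict between sections, which is in the published text, or the fact that 80% power is stated for one unadjusted test and then relied on for a hypothesis with three primary outcomes. An adjustment in another document would leave both in place.

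**Conclusion.** The point holds in this limited form. The primary outcome is stated inconsistently, and the stated 80% power belongs to a single test at an unadjusted 5%. The reproduction of 162 and 96 from the article's own inputs makes the second part firm.

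The consequences are conditional. Under an any-of-three rule with each test at 5%, the family-wise error is about 14% if the composites are independent, about 12.5% at correlation 0.5 and 8 to 9% at 0.9. Under an all-three rule the error rate is safe, but power is about 52–54% to 73%. With Holm at a family-wise 5%, power per domain is at least 66% if f = 0.25 holds in that domain, and about 72–77% if it holds in all three. Both the success rule and the correlation are assumptions. The conclusion does not require that the trial actually lacks multiplicity control.

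**What to change.** 1. Make the Outcomes section agree with the abstract and the statistical section: the three domain composites are primary, and any overall composite is secondary. The reverse choice is not advisable. The article gives the overall composite no components or weights, nothing shows that f = 0.25 applies to it, and recruitment is already under way.
2. State the success rule: whether each domain supports its own claim or all three are required.
3. Test the three composites with Holm at a family-wise 5%, so that each domain can be claimed separately.
4. Restate power at N = 162: 80% for one unadjusted test, and at least 66% per domain under Holm, rising to about 72–77% if all three effects are f = 0.25.

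Do this before outcome data are compared by arm. The cost is a less favourable power statement. No participants, visits or measurements are added; the total of 210 in the working shows only what 80% per domain under plain Bonferroni would need.

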#### Rationale of computerized cognitive training

Computerized cognitive training (CCT) has benefits over other types of CT as it readily lends itself to home-based use and individualized training protocols. For example, a study including 42 patients with amnestic mild cognitive impairment (MCI) found training using a tablet computer to robustly improve episodic memory function, while additionally enhancing visuospatial abilities [8]. Although direct comparisons are difficult, a current meta-analysis indicates that computer-based interventions outperforms therapist-led trainings in MCI [18]. Comparing CCT by content, training of multiple-domains outperformed single domain trainings [19]. Multi-component CCT has beneficial effects on a number of cognitive aspects such as global cognition, attention, working memory [11] as well as processing speed [12] and delayed recall [13].

The ultimate goal of CT, transferring its effects to activities of daily life or cognitive tasks regarding different cognitive domains (far transfer), is particularly difficult to achieve when the trained task is too narrowly designed. Theoretical frameworks for the investigation of transfer effects have been established [20]. Interestingly, when examining predictors of transfer from WM training, lower baseline performance predicted higher gains [21]. That same study indicated that old age was associated with lower gains on visuospatial WM tasks.

Discordant conclusions concerning optimal training protocols also affect CCT interventions [22]. Existing studies indicate that CCT for elderly individuals is best done in groups at an institution setting rather than at home to ensure good adherence i.a. due to social affiliation. A meta-analysis focusing on intervention characteristics, showed that CCT yields greater effect sizes when trained more than 3 times per week (*p* = 0.042), more than 8 total training weeks (*p* = 0.003) and more than 24 training sessions (*p* = 0.040) [19, 23]. However, reviews on the current state of research highlight the inconclusiveness on the best training protocols and the necessity of comprehensive and longitudinal assessments of a broad range of cognitive functions, including generalization of benefits from trained tasks to other cognitive activities (far transfer) [6].

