## Discussion

As main goal, the present RCT focusses on the effectiveness of CCT protocols as well as their neuronal underpinnings while ensuring high adherence. From a scientific viewpoint, our study will provide new insights how well a CCT can improve performance on the targeted cognitive domains. Even relatively mild effects of CCT would have a substantial economic impact given to possibility of a wide implementation. Models established for the UK indicate that a symptomatic intervention which leads to a one-point increase in the mini-mental state examination (MMSE) [68] would reduce health costs by millions if applied early in the disease process even if the effects of the intervention would wear out completely over 3 years [7].

The study overcomes major short-comings of prior research projects: First, the design of the study combines individual at home training with the social aspect of group meetings, leading to high adherence due to the social affiliation. Moreover, having multiple cognitive assessments and follow-ups over a one-year period allows analysis of longitudinal benefits of the training (e.g., duration of possible CCT effects). Additionally, the intervention group receiving a daily training over 9 months will help to assess possible dose-response relationships. Loss of motivation and thus declining training adherence was one of the major shortcoming of previous studies. We addressed this through the appealing design of the games, specifically tailored to please older players. Also, the interplay of at home training and repeated and frequent group meetings is thought to play a crucial role in keeping regimen adherence and motivation high.

Additionally, the study implements recommendations [9] for further RCTs conducted on this matter, e.g., by applying treatments to a rather heterogeneous sample (e.g., with respect to age range and wide range of symptom severity), using both an active as well as in waitlist control group, adding behavioural and biological markers, combining self-assessments and clinical assessments as outcome variables and following standardized protocols. Beyond this, we added follow-up visits after study completion to gain insight into long-term effects of our interventions that are both clinically and economically relevant.

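### The primary two-visit repeated-measures ANOVA can be biased if loss before 3 months is related to baseline score differently by arm, while the mixed model the plan itself prefers for missing data is kept for further analyses

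*Protocol article*

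**What the plan says.** The Sample size section poses the primary question as "Does change in performance on the three typical AD domains 3 months after the start of the training differ between groups" and answers it with this design: "a repeated- measures ANOVA is planned (3 groups with 2 time points", giving 162 participants, 54 per arm. The section on statistical methods for primary and secondary outcomes confirms the choice and gives power as the reason: "The main hypothesis will be tested with a repeated-measures ANOVA for which an adequate level of power should be guaranteed".

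The next sentence gives the mixed model a different role: "Further analyses (using all time points and additional numeric subject characteristics as predictor variables) will be performed with linear mixed models". The reason offered for it is that the article regards "linear mixed models as they allow for more sophisticated model design and a better handling of missing data". No missing-data method is named for the primary ANOVA.

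The same section drops non-adherent participants from analysis. It defines them as completing under 50% of training sessions and attending under 70% of group sessions.

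**The concern.** A standard repeated-measures ANOVA on two visits is a comparison of change scores, so a participant without the 3-month battery contributes nothing, not even the baseline. The article recognises that mixed models cope better with missing data, yet does not use one where the trial's main conclusion is drawn.

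The burden before 3 months is unequal. CCT asks for 50 home sessions and weekly meetings, the active control is matched for time and frequency, and the waitlist arm waits passively. The sample runs from subjective decline to mild Alzheimer's disease (MoCA above 11), so loss related to baseline level is plausible. The background section also cites a working-memory training study in which "lower baseline performance predicted higher gains", so the mix of baseline levels among completers matters for change. If that mix shifts differently by arm, the primary contrast shifts too. The primary ANOVA and the four-visit mixed model could then give different 3-month answers, because they would rest on different participants.

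**Working it through.** **1. The plan's own figures.** Inputs from Sample size: k = 3 groups, f = 0.25, α = 5%, power 80%; m = 2 visits for the primary test. The noncentrality is λ = f²(N − k)(m − 1)ε. With N = 162 and ε = 1, λ = 0.0625 × 159 = 9.94 on 2 and 159 degrees of freedom, and power is 0.805. With m = 4 and ε = 0.75 the same formula gives N = 96. Both stated figures reproduce.

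**2. Does the power rationale require an ANOVA?** No. On complete two-visit data the group-by-time F is the one-way F on change scores, whichever model is fitted (for a random-intercept model, provided its variance estimate is not at the boundary). On one simulated complete data set (3 × 54) both the ANOVA and the random-intercept mixed model gave F = 6.7216.

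**3. When are completers biased?** Let the 3-month score be r × baseline + a practice effect common to all arms + noise, with SD 1 at each visit and no true CCT effect. If dropout depends only on arm and baseline,

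bias = −(1 − r) × (mean baseline of CCT completers − mean baseline of control completers).

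So dropout rates that merely differ by arm give no bias. Nor are unequal rates necessary: with 15% loss in both arms, related to baseline in CCT only, the simulated bias at r = 0.5 is −0.065 SD.

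**4. Size.** The article gives neither dropout rates nor the visit correlation, so these are assumptions: 5% dropout in controls, 15% or 25% in CCT, low scorers more likely to leave (odds ratio 2.7 per SD), 2 million simulated participants per arm. Bias of the completer contrast, in baseline SD:

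| r | baseline-related in both arms, CCT 15% / 25% | baseline-related in CCT only, CCT 15% / 25% |
|---|---|---|
| 0.5 | −0.043 / −0.083 | −0.066 / −0.107 |
| 0.7 | −0.025 / −0.050 | −0.040 / −0.064 |
| 0.8 | −0.017 / −0.033 | −0.026 / −0.043 |
| 0.9 | −0.009 / −0.016 | −0.013 / −0.021 |

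The last column agrees with the formula. At r = 0.5, −0.107 implies a baseline shift of 0.107/0.5 = 0.214 SD, and 0.3, 0.2 and 0.1 times 0.214 give 0.064, 0.043 and 0.021. With dropout by arm only, the bias is within 0.001 SD of zero. The likelihood mixed-model estimate is also within 0.001 SD of zero throughout the table.

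**5. Against the design effect.** If CCT differs equally from both controls, f = 0.25 means a difference of 0.25 × 3/√2 = 0.530 SD of change, or 0.530 × √(2(1 − r)) baseline SD: 0.530, 0.411, 0.335 and 0.237 for r = 0.5, 0.7, 0.8 and 0.9. The largest bias at each r is then 0.107/0.530 = 20%, 0.064/0.411 = 16%, 0.043/0.335 = 13% and 0.021/0.237 = 9%. The smallest entries give 8%, 6%, 5% and 4%.

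**6. At the trial's own size.** 6000 simulated trials per scenario, 54 per arm, no true effect, dropout of 20% (CCT), 10% (active control) and 5% (waitlist), r = 0.5-0.8:
- baseline-related in CCT only: bias −0.10 to −0.04 SD, omnibus type I error 5.8-7.1%;
- same baseline dependence in all arms: bias −0.06 to −0.03 SD, type I error 5.2-5.9%;
- arm only: bias 0.00, type I error 4.5-5.5%.

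The standard error is 0.12-0.18 SD. In the CCT-only scenario, the mixed-model estimate has bias of at most 0.003 SD and essentially the same standard error.

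**7. Limits of the remedy.** If dropout depends on the unobserved 3-month score, the ANOVA is off by +0.01 to +0.08 SD and the mixed model by +0.02 to +0.13 SD. If the baseline slope in CCT is lower by an assumed 0.2, a mixed model with pooled covariance keeps a bias of −0.02 to −0.03 SD.

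**The case against.** The ANOVA is conventional, matches its power calculation, and is followed by mixed models over all visits, which include the 3-month visit. Several stronger readings are tempting but lack support.

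- *The article discards incomplete participants.* It does not say so. Complete-case use is inferred from how the test is normally run, and an analysis plan not shown could add imputation.
- *The article predicts loss of motivation in this trial.* The sentence "Loss of motivation and thus declining training adherence was one of the major shortcoming of previous studies" concerns earlier studies. The article goes on to say that the game design addresses this, and its Objectives expect high adherence. Poor training is also not the same as a missed assessment.
- *Unequal dropout alone biases the result.* It does not (steps 3 and 6).
- *The ANOVA would too often declare CCT beneficial.* In the CCT-only scenario of step 6 the bias runs against CCT: significant omnibus results with CCT ahead of the controls' mean fall to 1.0-1.2%, against about 2.5% with arm-only dropout. The direction would reverse if low scorers declined more instead of gaining more.
- *The mixed model is a complete cure.* Step 7 shows that it is not.

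The non-adherence exclusion also stands as an objection to changing the model alone. Someone who leaves CCT early meets both criteria and is removed under either model. The passive waitlist arm has no sessions to miss before 3 months, so the rule selects only in the two active arms and is a more direct source of arm-dependent selection.

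What survives is that the article itself chooses the primary test, and its stated reason does not favour the ANOVA.

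**Conclusion.** The point holds in a limited form. The primary test is, as normally run, a completer analysis, and it can be biased if loss before 3 months is related to baseline score differently by arm. The size is about 0.01-0.11 baseline SD, or 4-20% of the difference implied by f = 0.25 when CCT differs equally from both controls. This rests wholly on assumed dropout rates, dropout mechanisms and visit correlations; the documents supply none of them. A likelihood mixed model removes or largely removes this bias. The gain is in validity, not precision, and it does not extend to dropout driven by the unobserved outcome. It is a worthwhile and inexpensive improvement, not a defect that invalidates the trial.

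**What to change.** In the section on statistical methods for primary and secondary outcomes:

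1. Make the primary test the 3-month group-by-time contrast from a linear mixed model (ML or REML, unstructured two-visit covariance, site included), fitted to all randomised participants with any baseline or 3-month composite.
2. State that the non-adherence exclusion does not apply to this analysis and is used only in a per-protocol sensitivity analysis.
3. Keep the completer ANOVA as a sensitivity analysis.
4. Add a sensitivity analysis for data missing not at random.

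The calculation in Sample size can stand, with a note that the two F tests coincide on complete data. No new participants, visits or measurements are needed. Mixed models are already planned, although the article does not say that any has been programmed. The cost is slightly more analysis work, and an estimate that includes non-adherent participants and so may be smaller.
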